Eligibility Criteria

This study will involve Malaysian citizens employed as MMH workers in warehouses. Participants shall be at least 18 years old and regularly engage in MMH tasks such as lifting, lowering, pushing, pulling, carrying, holding, or restraining objects that exceed 14 kilograms, according to the National Institute for Occupational Safety and Health (NIOSH) guidelines 2015. They must work at least eight hours daily and perform these tasks as part of their routine responsibilities. Additionally, participants must have a mobile phone capable of downloading and using the MAKAR XR app. Those excluded from participation include pregnant individuals, anyone who has attended ergonomic training within the past six months, and interns or temporary workers.

Setting and Recruitment

The study takes place at two warehouses in the Klang Valley. We recognize differences between sites, such as task variety, shift schedules, and prior ergonomic training, which could influence the results. Recruitment is coordinated with each company's safety and health committee through invitation emails and letters, workplace posters, e-posters in departmental WhatsApp groups, and targeted phone calls. Interested workers are screened based on specific inclusion and exclusion criteria and are asked to provide their consent individually.

Allocation

To reduce cross-group contamination, allocation is non-randomized at the site/shift level: one warehouse is assigned to ARPE (intervention) and the other to guideline-based training (control). The site closer to HQ was pragmatically chosen for the intervention to ease monitoring; the second site serves as the control. The sites are geographically separated to minimize contact between groups. We acknowledge that differences between sites may confound the results; therefore, we will (i) document site characteristics (department mix, average load profiles, previous musculoskeletal disorder (MSD) initiatives), (ii) report baseline comparability using standardized mean differences (SMDs), and (iii) adjust analyses as described below.

Sample Size

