The sample size was determined from a previous study, which indicated a 57.5% improvement in knowledge [23]. In this study, 52.5% of participants demonstrated very good self-efficacy, while 85% reported perfect practice following the ergonomic training program (ETP) in the experimental group. This calculation utilized a 95% CI and an 80% power. The calculated sample size required was 28 participants per group. To account for a 40% attrition rate [24], an additional 11 participants were included, resulting in a final sample size of 39 participants per group informed by reports of high turnover in shift-based workforces [24]. Therefore, the total number of participants required for this study is 78, ensuring sufficient power to detect significant differences between the intervention and control groups while accounting for potential participant dropout.

Intervention

The study aims to enhance workers' understanding of ergonomics, increase awareness of WMSDs, promote a culture of workplace safety and health, and encourage the adoption of effective ergonomic practices. The ARPE module is based on scientific evidence, including literature, manuals, and guidelines aligned with the Department of Occupational Safety and Health (DOSH) for MMH workers. Its structure, which includes three domains and 25 subdomains, is summarized in Table 1. Operational steps are shown in Figure 1: eligibility screening and recruitment by warehouse; non-randomized, site-level assignment (Warehouse A: ARPE; Warehouse B: conventional training); baseline assessment at week 0; immediate post-knowledge assessment at week 1; and a follow-up evaluation at week 6 across all three domains, with withdrawals/losses to follow-up recorded. Participants in the intervention and control groups were recruited from separate warehouses to minimize cross-contamination, and subsequent statistical analyses were conducted as outlined in Figure 1.

**Table 1 TAB1:** Domains, variables, instruments/tools, timepoints, and purposes of assessment in the ARPE study t_0_: baseline (pre-intervention); t_1_: week 1 (post-knowledge evaluation); t_2_: week 6 (final follow-up) PQ: Perceived Risk; RQ: Reaction; SA: Self-Assessment; ARPE: Augmented Reality Physical Ergonomics

Domain	Variable	Instrument/tool	Timepoints	Purpose

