## Results

Planned outcomes and data analysis

Since this is a protocol, no results are available yet. The primary outcome is ergonomic knowledge, while secondary outcomes include self-prevention behaviors and self-evaluation, measured at baseline (T0), post-training (T1), and six weeks later (T2). Analyses will follow intention-to-treat principles using repeated-measures mixed models (fixed effects: group, time, group×time), with site effects and adjustments for baseline scores and prespecified covariates (e.g., age, tenure, department/shift, prior training). Two-sided α=0.05; results will be reported as adjusted mean differences with 95% CI. Sensitivity analyses will incorporate site-clustered standard errors (SEs), a random intercept for the site if applicable, and inverse-probability-of-treatment weighting. Outcome assessors and the statistician will remain blinded to group allocation. 

Protocol Status and Timeline

Recruitment and baseline assessments are ongoing; follow-up continues through November 2025, after which data will be cleaned and analyzed. No interim results are available.

Interpretation of Change

A structured outcome framework was created to assess the effectiveness of the ARPE training module. The assessments are divided into three domains: ergonomic knowledge (the primary outcome), self-prevention behaviors (secondary outcome 1), and self-evaluation skills (secondary outcome 2). Each domain is evaluated at three key timepoints: baseline (t_0_, before the intervention), week 1 (t1, after the intervention to assess knowledge), and week 6 (t2, follow-up post-intervention). The tools used are adapted from Diego-Mas et al. [14]. All scales are scored so that higher scores reflect better outcomes. The primary endpoint is the change in ergonomic knowledge from baseline to immediate post-training (T0→T1). ARPE will be considered superior if the adjusted group-time effect (ARPE-control) is positive with a 95% CI that does not include 0 (two-sided α=0.05); persistence will be evaluated at T2. For secondary domains (self-prevention, self-evaluation), adjusted group×time effects at T1 and T2 will be regarded as improvements when the 95% CI excludes 0; these analyses are exploratory and supportive.

Baseline Characteristics

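### The 80% power claim takes no account of allocating one whole warehouse per arm, so it holds only if change does not vary between warehouses

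*Protocol article*

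**What the plan says.** The Sample Size section starts from percentages in an earlier study: "The sample size was determined from a previous study, which indicated a 57.5% improvement in knowledge [23]". It adds that "52.5% of participants demonstrated very good self-efficacy, while 85% reported perfect practice following the ergonomic training program (ETP) in the experimental group". The only design settings it names are these: "This calculation utilized a 95% CI and an 80% power". The result follows: "The calculated sample size required was 28 participants per group". Eleven workers per group are added for attrition, giving 39 per group and 78 in total, and the section concludes that this number is "ensuring sufficient power to detect significant differences between the intervention and control groups while accounting for potential participant dropout".

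The Allocation section, just before it, states that "one warehouse is assigned to ARPE (intervention) and the other to guideline-based training (control)", without randomization. Setting and Recruitment says that the two sites differ in ways that could affect the results, and Allocation says that these differences may confound them.

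On analysis, Data Analysis sets out a GEE that clusters on participants, with site as a fixed effect. Planned outcomes and data analysis lists site-clustered standard errors and a random site intercept as sensitivity analyses, and fixes the error rate: "Two-sided α=0.05; results will be reported as adjusted mean differences with 95% CI". Baseline Characteristics also mentions cluster-robust standard errors. Interpretation of Change declares ARPE superior if the adjusted group-by-time effect is positive and its 95% confidence interval excludes zero.

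**The concern.** Allocation is by warehouse, but nothing in the sample size reasoning reflects that. Workers in one warehouse share supervisors, shift patterns and a safety culture, so their change over six weeks may be correlated. If it is, 28 workers in one warehouse carry less information about the training than 28 independent workers.

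Two things are at stake. The stated power may be too high. The superiority rule may also reject too often, because a standard error built from worker-to-worker variation omits the between-warehouse part. The protocol itself gives reasons to expect some site-specific change: the intervention site was chosen because it is nearer headquarters and easier to monitor, and local supervisors confirm participation.

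**Working it through.** **1. Can the 28 be reproduced?** No formula, comparator rate, difference or standard deviation is printed, so it cannot be confirmed. Routes tried, at 80% power and two-sided 5%:

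- 52.5% vs 85%, unpooled: (1.96 + 0.8416)² × (0.525×0.475 + 0.85×0.15) / 0.325² = 7.849 × 0.376875 / 0.105625 = 28.005. This is 28 if rounded and 29 if rounded up. The pooled version gives 31, and with continuity correction 37.
- 57.5% vs an unstated control rate of about 21.5%: 28.
- Two means differing by 0.75 SD, also unstated: 28.

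The first route is close, but 52.5% and 85% are two different outcomes (self-efficacy and practice) described for one group, so the match is unconfirmed. All these routes treat workers as independent.

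**2. What the planned model can separate.** With one site per arm, a design matrix with intercept, group, two time terms, two group-by-time terms and site has 7 columns but rank 6: site is fully aliased with group. The group-by-time contrast can still be estimated, and it removes stable site differences. It does not remove a difference between warehouses in how workers change. Between-site degrees of freedom are 2 × (1 − 1) = 0, so that variation cannot be estimated. Neither site-clustered standard errors nor a random site intercept can supply it.

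**3. Size, as an illustration.** Assumptions: 28 independent workers per arm give 80% power (equivalent to a difference of 2.8016 × √(2/28) = 0.749 SD); the site variance is known; the ICC is for change and is assumed, since the document gives none. With 28 analysed per arm:

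- Design effect: DE = 1 + 27 × ICC
- Effective n = 28 / DE
- Power = Φ(2.8016/√DE − 1.96)
- False-positive rate if workers are treated as independent = 2 × [1 − Φ(1.96/√DE)]

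| ICC | DE | Effective n | Power | False-positive rate |
|---|---|---|---|---|
| 0 | 1.00 | 28 | 80% | 5% |
| 0.01 | 1.27 | 22 | 70% | 8% |
| 0.02 | 1.54 | 18 | 62% | 11% |
| 0.05 | 2.35 | 12 | 45% | 20% |
| 0.10 | 3.70 | 8 | 31% | 31% |

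For example, at ICC 0.05: √2.35 = 1.533; 2.8016/1.533 − 1.96 = −0.132; Φ = 0.447.

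**4. If all 39 per arm were retained.** With DE = 1 + 38 × ICC and 2.8016 replaced by 2.8016 × √(39/28) = 3.306, power is 91% at ICC 0, 80% at 0.01, 70% at 0.02, 49% at 0.05 and 33% at 0.10. This needs no attrition at all, whereas the plan allows for 40%.

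**5. Can more workers recover the loss?** To match 28 independent workers, one site per arm needs m = 28 × (1 − ICC) / (1 − 28 × ICC):

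- ICC 0.01: 27.72 / 0.72 = 38.5, so 39
- ICC 0.02: 27.44 / 0.44 = 62.4, so 63
- ICC 0.03: 27.16 / 0.16 = 169.75, so 170
- ICC of 1/28 = 0.036 or more: the denominator is zero or negative, so no number is enough.

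**The case against.** The strongest reply is that the protocol is open about the weakness. Allocation and the Discussion name site-level confounding, residual confounding and cautious interpretation. Site-clustered standard errors are planned as a sensitivity analysis, and future cluster-randomized trials are recommended. All this stands. But these passages treat site as a source of bias or a modelling check, and none of them qualifies the power statement.

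A second reply is that the size of the loss rests on an ICC that nobody has given. That is right. The relevant ICC is for change, and because the contrast removes stable site differences, an ICC for the outcome level would overstate the loss. Nothing in the document supports 0.05 or 0.10 over 0.01. Only the direction is independent of this choice: any positive between-warehouse variance in change takes power at 28 per arm below 80%.

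Four stronger readings are tempting, and the document does not support them:

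- A reader might infer that 28 was computed from 52.5% vs 85%. The match is close but unconfirmed.
- A reader might infer that adding workers could never help. In the design-effect model this is true only from an ICC of about 0.036.
- A reader might take the power figures as those of a test with correct standard errors. With zero between-site degrees of freedom no such test exists; the figures assume a known site variance.
- A reader might conclude that the information is always far below 28. At ICC 0.01 it is 22.

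**Conclusion.** The point holds as an unsupported design claim; no printed number is shown to be miscalculated. The 80% power and the two-sided 5% error rate hold only if change does not vary between warehouses. The document does not state that premise, and its own remarks on site differences give reason to doubt it. Under the assumptions listed with the calculation, power at 28 analysed per arm falls to about 70% at an ICC of 0.01 and about 31% at 0.10, while the false-positive rate rises to about 8% and 31%. The power figures are on the optimistic side because they take the site variance as known. They also rest on the unverified premise that 28 independent workers give 80% power for the knowledge score. The sample size statement should be corrected, but the design need not be changed for this point.

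**What to change.** In Sample Size, replace the closing assurance of sufficient power with a statement that the 80% applies to an individual-level comparison and assumes no between-warehouse variation in change. Add a short table of power and false-positive rate over a range of ICCs for change, labelled as assumed values with a known site variance. In Interpretation of Change, state that the confidence intervals and the superiority rule are conditional on the two warehouses studied, because site-specific change cannot be separated from the effect of training.

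The cost is a few sentences and one small table, with no extra enrolment and no change to recruitment already under way. The downside is a less favourable stated power.

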To evaluate the ARPE module, we developed a multi-domain assessment battery that covers ergonomic knowledge (primary) and self-prevention and self-evaluation (secondary). The knowledge test was aligned with occupational ergonomics guidelines and translated into Malay (scored 0-100%). The behavioral instruments were adapted from Diego-Mas et al. and operationalized through PQ (Perceived Risk; 11 items: Concern, Control, Loads, Repetitiveness, Postures), RQ (Reaction; 6 items: Prior AR Exposure, Expectation, Interest, Usefulness), and SA (Self-Assessment; 7 items: Memory, Concern, Control), all using 7-point Likert scales with domain scores calculated as item means (higher scores indicate a greater presence of the construct) [14]. Translation and cultural adaptation were followed by assessments of content validity (Content Validity Index (CVI); 7 experts), face validity (Face Validity Index (FVI); 10 MMH workers), construct validity (Exploratory Factor Analysis (EFA); n=100), and reliability testing. For CVI, we applied standard acceptability criteria (Item-level Content Validity Index (I-CVI) ≥0.78; Scale-level Content Validity Index, average method (S-CVI/Ave) ≥0.90), consistent with recommended procedures in content validity studies [20]. For factorability, we required Kaiser-Meyer-Olkin (KMO) >0.60 and Bartlett's test p<0.05, with primary loadings ≥0.40. Internal consistency was considered acceptable at Cronbach's α ≥0.70, good at ≥0.80, and excellent at ≥0.90 (with corrected item-total correlations ≥0.30). Test-retest reliability was assessed using the intraclass correlation coefficient (ICC) (two-way, absolute agreement), with the following thresholds: <0.50 poor, 0.50-0.74 moderate, 0.75-0.89 good, and ≥0.90 excellent. 95% confidence intervals (CIs), standard error of measurement (SEM), and minimal detectable change at the 95% confidence level (MDC_95) will also be reported. In prior related studies, the scales demonstrated α coefficients ranging from 0.71 to 0.92 [14]. All analyses will be performed using IBM SPSS Statistics for Windows, Version 29.0 (IBM Corp., Armonk, New York, United States).

Phase 1b: usability outcome (ARPE (AR) mobile app usability)

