Baseline characteristics	Age, gender, ethnicity, education level, job category, years of service, shift work, work process	Self-administered questionnaire (Malay version)	t_0 _ (week 0: before intervention)	To describe participant demographics and work-related characteristics
Primary outcome	Ergonomic knowledge	Adapted Diego-Mas et al.'s PQ Questionnaire [14]	t_0_, t_1_,t_2_	To evaluate knowledge acquisition and the retention of ergonomic principles
Secondary outcome 1	Self-prevention	Adapted Diego-Mas et al.'s PQ Questionnaire [14]	t_0_, t_1_, t_2_	To assess the implementation of preventive ergonomic behaviors
Secondary outcome 2	Self-evaluation	Adapted Diego-Mas et al.'s RQ and SA Questionnaires [14]	t_0_, t_1_, t_2_	To assess awareness and self-assessment of ergonomic risks and practices

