Self-prevention (PQ-derived domain mean; 7-point Likert scale; higher scores indicate better performance; scores are rescaled from 0 to 100) will be analyzed using GEE (identity link, Gaussian), clustering on participants with robust (sandwich) SEs and an exchangeable working correlation. The model includes group (ARPE vs. control), time (t_0_, t_1_, t_2_), group×time, site (fixed effect), and prespecified covariates (age, tenure, department/shift, prior training). Between-group change is tested via group×time with prespecified contrasts reporting marginal ARPE-control differences at t_1_ and t_2_ with 95% CI (two-sided α=0.05) and SMDs. Within-group change (t_1_-t_0_, t_2_-t_0_) will be presented using model-based marginal contrasts (descriptive). Missing data will be addressed under MCAR/MAR using GEE with robust SEs; sensitivity analyses will include inverse-probability-weighted GEE.

Secondary Outcome 2: Self-Evaluation 

Self-evaluation will be assessed using adapted RQ and SA domain means (7-point Likert scale; higher scores indicate better performance; scores are rescaled from 0 to 100). Repeated measures (t_0_, t_1_, t_2_) will be analyzed with GEE using an identity link and Gaussian family, clustering on participants with robust (sandwich) SEs and an exchangeable working correlation (Quasi-likelihood under the Independence model Criterion (for comparing GEE correlation structures) (QIC) to compare AR(1) and unstructured). The model includes group (ARPE vs. control), time, the interaction between group and time, site (fixed effect), and prespecified covariates (age, tenure, department/shift, and prior training). Between-group differences will be tested via the group×time interaction, with prespecified contrasts reporting marginal ARPE-control differences at t_1_ and t_2_ (95% CI; two-sided α=0.05; SMDs shown). Within-group changes (t_1_-t_0_, t_2_-t_0_) will be derived from model-based marginal contrasts (95% CI) and presented descriptively; inference will follow the GEE model.

Data Collection

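### The primary outcome has two incompatible instruments: Table 1 names the PQ perceived-risk questionnaire, also used for secondary outcome 1, while the methods describe a separate 0-100% knowledge test

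*Protocol article*

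**What the plan says.** **Table 1.** The rows for ergonomic knowledge (primary) and self-prevention (secondary outcome 1) carry the same tool entry, the adapted "PQ Questionnaire [14"]. The stated purpose of the primary row is "To evaluate knowledge acquisition and the retention of ergonomic principles". The legend reads "PQ: Perceived Risk; RQ: Reaction; SA: Self-Assessment".

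**Assessment Tool Development and Validation.** Two kinds of tool are described. The first is a test: "The knowledge test was aligned with occupational ergonomics guidelines and translated into Malay (scored 0-100"%). The second is a set of behavioral instruments adapted from the cited instrument study [14], among them "PQ (Perceived Risk; 11 items: Concern, Control, Loads, Repetitiveness, Postures"). These are scored differently from the test: "all using 7-point Likert scales with domain scores calculated as item means". A higher score is said to mean more of the construct.

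**Interpretation of Change (Results).** After listing all three domains, this section says that the tools are adapted from source [14]. It adds: "All scales are scored so that higher scores reflect better outcomes". It also defines the primary endpoint as the change in ergonomic knowledge from T0 to T1 and sets the superiority rule on the adjusted group-time effect for it.

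**Secondary Outcome 1.** "Self-prevention (PQ-derived domain mean; 7-point Likert scale; higher scores indicate better performance", with scores rescaled to 0-100.

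**Data Analysis.** Ergonomic knowledge is analysed on a 0-100% scale.

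**The concern.** A protocol has to leave no doubt about which score is the primary endpoint. Here two parts of the article point to a perceived-risk questionnaire and another part points to a knowledge test.

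If the trial is run from Table 1, the primary question (does ARPE raise ergonomic knowledge more than guideline-based training?) would be answered with Likert ratings of perceived risk. The purpose that Table 1 itself gives for the row would then not be met by the knowledge test built for it. The first secondary outcome would come from the same questionnaire, so it would offer little separate support.

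Timing adds to this. Protocol Status and Timeline says that recruitment and baseline assessments are ongoing. A worker who completed only the PQ at baseline has no baseline knowledge score, and a T0 to T1 change in knowledge cannot be recovered for that worker later.

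**Working it through.** No stated figure is at issue, so the check sets the passages side by side.

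| Place | Ergonomic knowledge (primary) | Self-prevention (secondary 1) |
|---|---|---|
| Assessment Tool Development and Validation | Separate guideline-aligned test, 0-100% | Behavioral instruments from source [14], including the PQ |
| Table 1 | Adapted PQ | Adapted PQ |
| Interpretation of Change | Tool adapted from source [14] | Tool adapted from source [14] |
| Secondary Outcome 1 | not addressed | PQ-derived domain mean, rescaled to 0-100 |
| Data Analysis | 0-100% scale, instrument not named | Same GEE approach, instrument not named |

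1. **Is it an extraction fault?** No. Both Table 1 rows are intact and legible, and their tool entries match word for word.

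2. **Is it one mistyped cell?** Not only. Interpretation of Change attributes the tools of all three domains to source [14], which agrees with Table 1. In the tool-development section only the behavioral instruments come from that source, and the knowledge test is tied to ergonomics guidelines.

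3. **Does the analysis text settle it?** Only in part. Secondary Outcome 1 uses the PQ for self-prevention, which fits the tool-development section. The 0-100% scale in Data Analysis fits the knowledge test, but it does not exclude a rescaled PQ. Assuming the usual linear rescaling of a 1-7 item mean m, (m - 1) / 6 × 100, a mean of 1 gives 0, a mean of 4 gives 50 and a mean of 7 gives 100. Both candidate scores therefore run from 0 to 100, and the range alone does not identify the instrument. The separation rests mainly on the tool-development section.

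4. **Could both descriptions be true?** Not as written. One score is a test result in percent and the other is a mean of 7-point ratings. No passage says that the knowledge test is part of the PQ, or that particular PQ items form a knowledge score.

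5. **How many participants could be affected?** The documents do not say which form is in use. The number without a baseline knowledge test could be anywhere from none to everyone enrolled so far, with the planned total of 78 (39 per group) as the ceiling.

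6. **Direction of the PQ.** The tool-development section says that a higher score means more of the construct, which for the PQ is perceived risk. Interpretation of Change and Secondary Outcome 1 say that higher is better. A direction is therefore stated, but the article does not explain why more perceived risk is better self-prevention. Nor does it explain how such a rating serves Table 1's purpose for that row, which is whether preventive behaviors are put into practice.

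**The case against.** The best defence is that this is a drafting slip in one row. The tool-development section and Secondary Outcome 1 give a coherent picture (knowledge test for the primary, PQ for self-prevention), and Data Analysis is compatible with it. That is the likeliest intention. It does not remove the conflict, because Interpretation of Change repeats the Table 1 version and nothing reconciles the two.

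A reader might also draw stronger conclusions, which the article does not support:

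- **That the primary and first secondary outcomes would be one score, correlated at 1.0.** Table 1 names an instrument, not a scoring rule. The PQ has five subdomains, and the two rows could draw on different items. What stands is that the same instrument is named and no separate scoring is given.
- **That the PQ cannot measure knowledge or behavior at all.** The items are not shown. The label, the subdomain names and the Likert format justify doubt, but not a flat denial.
- **That the sign of the self-prevention effect is undefined.** Two sections say that higher is better, and raising awareness of musculoskeletal disorders is a stated aim of the training, so higher perceived risk may be the intended direction. Item-level scoring keys may sit in a fuller document. What stands is a request for the rationale.

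**Conclusion.** The point holds as an internal contradiction about the primary endpoint and must be corrected. The superiority rule rests on a score that the article defines in two incompatible ways. Under Table 1 that score is a perceived-risk rating from the same instrument as secondary outcome 1. Under the tool-development section it is a separate knowledge test.

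The contradiction itself rests on the text alone and needs no assumption about item content. The practical consequence depends on which form is being administered, which the article does not state. If the knowledge test is in use at every timepoint, the error is one of wording. If only the PQ is in use, the T0 to T1 knowledge change is lost for the workers already assessed.

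The question of PQ direction and interpretation is secondary. It calls for a justification and a suitably limited conclusion, and does not show that the analysis of self-prevention is invalid.

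**What to change.** 1. In the primary-outcome row of Table 1, replace the PQ with the guideline-aligned Malay knowledge test (0-100%) at t0, t1 and t2. Keep the PQ for secondary outcome 1 only.
2. In Interpretation of Change, restrict the statement about source [14] to the behavioral instruments. If only the table is edited, the contradiction survives.
3. Confirm at once which form participants at both warehouses are completing. If it is not the knowledge test, correct it for the assessments still to come, and report by group how many participants have no baseline knowledge test.
4. Lesser point, before data lock: state why a higher PQ score counts as better self-prevention, and limit any conclusion about preventive behaviors to what the PQ measures. Renaming the outcome is optional.

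Items 1, 2 and 4 are changes of wording, since the knowledge test is already described as developed. Item 3 costs a check of the forms in use. If the wrong form has been used, the cost is lost baseline data that rewording cannot restore, and it grows with each further enrolment.
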